### Statistical analysis and reporting

Data will be reported and presented in accordance with the updated CONSORT criteria [30]. Children will be analysed according to allocation status (regardless of subsequent management). Clinical improvement will be defined by comparing: (a) the proportions of children who are cough free; and (b) the difference in PC-QOL at week 6 (with the intervention group being managed according to the pathway for at least 4 weeks). Efficacy of the clinical management pathway will be determined by improvements in both QOL measures and the percentage of children with a primary diagnosis achieved. Reliability will be determined by agreement in the implementation at each step of the pathway in children who have their medical records were re-examined. A kappa value of >0.6 will be considered acceptable for clinical practice (as recommended) [31]. Validity of the clinical pathway will be assessed by clinical failure rate (defined above), diagnosis reached by 12 months, and rates of misdiagnosis.

Unpaired and paired Student's T test will be used for continuous data comparisons (assuming normal distribution) and ANOVA utilised when >2 groups are compared. If data are not normally distributed, non parametric tests will be substituted. Chi squared tests will be used for categorical data. The 95% confidence intervals of all differences between the 2 study groups will be described.

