### Definitions used for clinical management pathway

• Asthma: Recurrent (>2) episodes of wheeze and/or dyspnoea that responds (within mins) to inhaled beta_2 _agonist, or bronchodilator resposiveness documented on spirometry (≥12% change in FEV_1 _%predicted after 400 ug salbutamol).

• Cough resolution: Improvement of ≥75% or total resolution according to cough diary data for ≥3 consecutive days [19,20]. When cough diary data are unavailable, resolution is defined as total cessation of verbal reporting of cough.

• CXR abnormality: Any abnormality (other than peribronchial thickening) as interpreted by specialist (respiratory or radiology).

• Primary diagnosis of aetiology of cough: Diagnosis confirmed by subsequent specific treatment which resulted in cough resolution within the expected time frame of <3weeks[20,21] (see above for time frame chosen). Diagnostic criteria are defined a-priori as published [22].

• Protracted bronchitis: (a) Presence of isolated chronic moist cough; (b) Resolution of cough with appropriate antibiotics; and (c) absence of an alternative cause for specific cough [20].

• Recurrent protracted bronchitis: ≥3 episodes per year of protracted bronchitis.

• Reversible airway obstruction: In accordance with American Thoracic Society and European Respiratory Society criteria with Australian predicted values used [23].

• Secondary diagnosis: Diagnosis found on objective tests but which: 1) specific treatment did not result in resolution or improvement of the cough; or 2) no treatment for this diagnosis was trialled and the cough resolved with other treatment or spontaneously [22].

• Specific cough pointers: Presence of any of the following- auscultatory abnormality, classical cough characteristics, cardiac abnormalities, chest pain, chest wall deformity, daily moist or productive cough for >3 months, digital clubbing, dyspnoea (exertional or at rest), failure to thrive, feeding difficulties (including choking/vomiting), haemoptysis, immune deficiency, neurodevelopmental abnormality, recurrent pneumonia, wheeze. These pointers are explained in TSANZ position statement [20].

• Spirometry abnormality: As determined by the American Thoracic Society and European Respiratory Society criteria with Australian predicted values used [23].

• Tertiary hospital management: Management that usually requires the level of investigations at a paediatric tertiary centre (bronchoscopy, chest HRCT scan, fluoroscopic swallowing screening, etc).

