### The rationale for the clinical pathway being studied and study outcome measures

Our clinical management pathway is based on:

• Systematic evaluation of the evidence with low susceptibility to bias updated from previous publications (in particular relevant Cochrane Reviews)[22]

• Definitions and key management approaches used in the Thoracic Society of Australia and New Zealand Position Statement [20].

• The findings of previous research on cough in children where we have shown that dry cough is more likely to resolve naturally [19].

• Where no evidence exists, management is based on clinical experience (approximately 250 doctor-years in total).

Objective cough monitoring is the gold standard for cough studies [27]. However in a clinical multi-centre study, cough monitors are not feasible. It is also arguable that QOL measures are more clinically relevant [32]. Thus we have chosen a parent cough-specific QOL (PC-QOL) [25]. Since the presence of cough influences QOL [33], the time taken for cough resolution is also a clinically important outcome.

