### Limitations of our study

In addition to the lack of an objective measure of cough as an outcome measure, our study could not be performed as a double blinded study. Ideally, the RCT should involve the use vs. non-use of the clinical pathway and assess both short-term and long-term outcomes. However, our studies over the last decade have already influenced practice. Most specialists would not feel comfortable withholding investigation and treatment for a prolonged period. We have therefore designed a RCT to assess short-term outcomes only (at 6 weeks after initial referral). This is acceptable given the usual waiting time to see a specialist. Importantly, our design also allows us to assess short-term harm that might be associated with early referral (such as over-investigation and treatment of a spontaneously resolving illness).

In summary, this will be the first multicentre study (conducted in 5 major Australian cities) to examine the effectiveness of an evidence-based clinical pathway for the management of chronic cough in children.

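### A cough that clears without specific treatment counts as no primary diagnosis, so part of the efficacy statement cannot tell untreated recovery from failure to find a cause

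*Protocol article*

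**What the plan says.** Under Statistical analysis and reporting, the pathway's efficacy is to be judged on gains in the two QOL measures and on "the percentage of children with a primary diagnosis achieved". Under Outcome measures, the proportion with a primary diagnosis is a secondary outcome; the primary outcomes are the proportion cough free and the PC-QOL difference at week 6.

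The section Definitions used for clinical management pathway gives the rule for a primary diagnosis: "Diagnosis confirmed by subsequent specific treatment which resulted in cough resolution within the expected time frame of <3weeks". The same section deals with recovery that followed no treatment for a finding. An objective finding is only a secondary diagnosis when "no treatment for this diagnosis was trialled and the cough resolved with other treatment or spontaneously". It adds: "Diagnostic criteria are defined a-priori as published".

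Three other places treat natural recovery as expected or acceptable:
- The rationale section lists among the foundations of the pathway "The findings of previous research on cough in children where we have shown that dry cough is more likely to resolve naturally".
- The Discussion names watchful waiting among the management approaches on which evidence is needed.
- The limitations section says the design can assess short-term harm of early referral, with the example "over-investigation and treatment of a spontaneously resolving illness".

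**The concern.** The diagnosis percentage is read as better when higher. Under the printed definition, a child observed without specific treatment who gets better cannot raise it. The same child, if treated and recovering by chance inside the three-week window, does raise it. The first child is counted exactly like one in whom the pathway was tried and no cause was established.

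Two things are at stake. One component of the efficacy statement mixes a good result (recovery without treatment) with a poor one (no cause found). And because the arms enter the pathway at different times, the measure can differ between them through opportunity to treat alone. That would obscure the over-treatment harm the article says the design can examine.

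**Working it through.** **What the text fixes.** Take four kinds of child and apply the printed definitions.

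| Course | Cough free | Primary diagnosis |
|---|---|---|
| Specific treatment, cough resolves in under 3 weeks | yes | yes |
| No specific treatment, objective finding, cough resolves | yes | no (secondary only) |
| No specific treatment, no objective finding, cough resolves | yes | no (no class) |
| Cough persists, no cause confirmed | no | no |

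Rows 2 and 3 share the diagnosis result of row 4. The End point section offers no separate class either: participation ends with diagnosis plus resolution, with an exit criterion, or at 12 months.

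**Arms.** Under Intervention and follow up, active children enter the pathway within 2 weeks of consent and controls at 6 to 8 weeks. A control child whose cough clears while waiting has had no pathway treatment to confirm a cause. An active child with the same natural course may have been treated by then.

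**The plan's own figures.** The plan gives no figure for the diagnosis rate. The nearest number is the 35% in the Sample size section. That power statement reproduces with 110 per arm (1:1 assumed), 35% versus 55%, two-sided 5% (assumed) and a continuity correction:
- null standard error = √(2 × 0.45 × 0.55 / 110) = 0.0671
- alternative standard error = √((0.35 × 0.65 + 0.55 × 0.45) / 110) = 0.0657
- z = (0.20 − 1/110 − 1.96 × 0.0671) / 0.0657 = 0.904, power 81.7%, against 82% stated (85.1% without the correction).

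So the 35% is a planning rate for resolution by week 6 without the pathway. The Abstract describes that arm as receiving existing care, so it is not a rate of untreated recovery. It cannot supply the input below.

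**Illustration, all inputs assumed.** Let *s* be the share whose cough would clear naturally, *t* the share of those who are given specific treatment and credited with a diagnosis, and *g* the diagnosis rate among the rest, set to 80%.

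Diagnosis rate = *s·t* + (1 − *s*)·*g*. With equal *s* and *g* in two groups, the gap is *s* × (difference in *t*).

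| *s* | *t* = 0 | *t* = 0.5 | *t* = 1 | Gap, 0 v 0.5 | Gap, 0 v 1 |
|---|---|---|---|---|---|
| 20% | 64% | 74% | 84% | 10 points | 20 points |
| 35% | 52% | 69.5% | 87% | 17.5 points | 35 points |
| 50% | 40% | 65% | 90% | 25 points | 50 points |

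With 110 per arm, a two-sided 5% comparison would declare the *t* = 0 versus 0.5 gap significant with power 36%, 76% and 97% in the three rows. For *t* = 0 versus 1 the power is 93% to nearly 100%. Cough outcome is the same throughout. The last column is an extreme: both arms follow one pathway, so a full watch-all versus treat-all contrast is not what the trial compares.

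**The case against.** The strongest reply has four parts.

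1. *Both primary outcomes credit untreated recovery*, and the article defines clinical improvement by them. The efficacy sentence also includes the QOL measures, and recurrence related to the original diagnosis is tracked as possible misdiagnosis. This stands. A reader might infer that the trial's efficacy conclusion would be turned round; the text does not support that.
2. *Requiring a treatment response is a conservative way to confirm a cause.* This stands as a reason to keep the definition. It does not justify counting untreated recovery with failure to find a cause.
3. *The class may exist elsewhere.* The published diagnostic criteria are cited but not shown, nor is Figure 1, which covers non-specific cough. This stands and limits confidence. The printed definitions, outcomes and analysis text contain no such class.
4. *No size can be given.* This also stands. It is tempting to take the 35% as the natural-resolution rate and say the diagnosis percentage is capped at 1 − 0.35 = 65%. That rate is resolution under existing care, and no target percentage is set that such a cap would miss.

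A reader might also apply the treatment rule to the validity measure, diagnosis reached by 12 months. The article attaches the rule to *primary* diagnosis and lists the 12-month item separately, so that extension is inference.

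**Conclusion.** The concern holds in a limited form. On the printed text, the diagnosis component of the efficacy statement does not separate untreated recovery from failure to find a cause, and it can favour whichever arm treats earlier without any difference in cough outcome. It affects one secondary outcome and the efficacy statement, not the two primary outcomes.

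The size is unknown. The 10 to 25 point gaps for a half-share difference in treatment rest on assumed natural-resolution rates of 20% to 50%, equal in both arms, an assumed 80% diagnosis rate among the remaining children, and full credit for treated children who would have recovered anyway. The conclusion also assumes that the cited criteria and the figures do not already provide a class for natural recovery. It is worth correcting because the remedy is cheap and the article itself calls treatment of such illness a harm it can assess.

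**What to change.** Add an outcome class, 'cough resolved without specific treatment', to the definitions, the secondary outcomes and the analysis section. Make three mutually exclusive categories: primary diagnosis achieved, resolved without specific treatment, neither. Report all three by arm with every randomised child in the denominator, and read the efficacy statement on the first two together. If the cited criteria already hold this class, say so and carry it into the outcomes.

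Under the illustration, the 'neither' category is (1 − *s*)(1 − *g*) = 16%, 13% and 10% for *s* = 20%, 35% and 50%, whatever *t* is. The three categories therefore remove the spurious gap in diagnostic failure and leave the difference in treatment visible. They cannot show which treated children would have recovered anyway.

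Do not drop the untreated recoveries from the between-arm denominator. Recovery before treatment happens after randomisation and depends on allocation, since controls wait longer. If, say, 35% of controls and 15% of active children were removed (assumed), 110 × 0.65 ≈ 72 would be compared with 110 × 0.85 ≈ 94, and the groups would no longer be those randomised. That conflicts with the article's analysis by allocation. A percentage among children who did not resolve untreated may be given as description only.

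Cost: one coding rule and a three-category secondary outcome. Deciding whether a primary diagnosis was achieved already requires knowing what treatment was given and when the cough resolved. No rule on when to treat is changed.

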### Randomisation, allocation and blinding

The randomisation sequence was computer generated and used permutated blocks (4 or 6 participants per block). Children are randomised within two age strata (≤6years and >6years) and 5 site strata (Brisbane, Melbourne, Sydney, Canberra and Darwin). In Darwin, children are also be stratified by Aboriginality (as Aboriginal children in the Northern Territory are at an increased risk of chronic respiratory disease) [17]. The allocation sequence is concealed from all the investigators, participants and caregivers as done previously [18]. All primary outcome data are collected by telephone or by interview. The participants are informed (at each contact) that the person they speak to on the telephone should only be provided with direct answers to their questions. They are also advised that they can ring the clinical research staff directly if they need any additional information. The research nurse responsible for the primary outcome data collection received training on how to ensure the validity of clinical measurements. Through these means, we are confident that the person collecting the primary outcome data remain unaware of the allocation status of the participating child (outcome assessor blinded).

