#### Data collection

All data are collected on standardized forms. Outcomes (PC-QOL and PedsQL) are collected at times weeks 0 (baseline), 6, 10, 14, 26, 52 and at study endpoint. Additionally, daily cough diary scores are collected till cough resolves. Demographic data (smoking, anthropometry, etc) and medical details are collected at baseline.

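### Both primary analyses leave out baseline PC-QOL and the randomisation strata, so the intervals are wider than the collected data allow; the normality switch could also move the PC-QOL test off the mean difference used for sizing

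*Protocol article*

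**What the plan says.** The section *Statistical analysis and reporting* names the tests. For continuous data, whether unpaired or paired: "T test will be used for continuous data comparisons (assuming normal distribution". Then: "If data are not normally distributed, non parametric tests will be substituted". For proportions: "Chi squared tests will be used for categorical data". It adds: "The 95% confidence intervals of all differences between the 2 study groups will be described". It mentions no covariate and no stratification factor, and it gives neither a criterion for non-normality nor the name of the substitute test.

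Two other sections describe information that these tests do not use:

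- *Randomisation, allocation and blinding*: "Children are randomised within two age strata", within five sites, and in Darwin also by Aboriginality. The reason given for the Darwin factor is a raised risk of chronic respiratory disease. Blocks are of 4 or 6.
- *Data collection*: "Outcomes (PC-QOL and PedsQL) are collected at times weeks 0 (baseline), 6, 10, 14, 26, 52 and at study endpoint".

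The two primary outcomes, under *Outcome measures*, are the proportion cough free and the difference in PC-QOL, with week 6 as the time point. *Sample size* plans on 35% v 55% cough resolution with 220 children (82% power), and on a PC-QOL difference of 1 with SD 1.05 and 25 per group (91% power).

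**The concern.** There are three linked points.

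1. **Baseline PC-QOL is measured but not used.** A child's week-6 score is likely to track the baseline score. A two-sample t test leaves that shared variation in the error term. The paired t test does not help, because it addresses change within a group and not the contrast between groups.
2. **The strata shape the design but not the analysis.** Blocking within strata balances the arms on those factors. If the factors are prognostic, the true sampling variance of the difference is smaller than an unstratified test assumes, so the test is conservative and the interval too wide. The protocol itself treats at least one stratum as prognostic.
3. **The PC-QOL test depends on the look of the data.** The trial is sized on a mean difference. A rank test addresses a shift or ordering between distributions. If the switch is triggered, the primary p-value no longer refers to the quantity used for sizing.

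What is at stake is the width of the primary intervals, some power on the cough-free outcome, and whether test and estimate match for PC-QOL.

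**Working it through.** **Inputs.** From *Sample size*: N = 220, 35% v 55%, PC-QOL difference 1, SD 1.05, 25 per group, 5% significance. Assumed: two-sided testing, 1:1 allocation (110 per arm), all children observed, and 1.05 as the SD of the week-6 score. The article gives no baseline to week-6 correlation *r* and no stratum effects, so both are shown as ranges.

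**Step 1: reproduce the stated powers.**

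- PC-QOL, 25 per group, unadjusted: 91.0% by noncentral t (92.0% by normal approximation). Stated: 91%.
- Cough free, 110 per arm: null SE = √(0.45 × 0.55 × 2/110) = 0.0671; alternative SE = √((0.35 × 0.65 + 0.55 × 0.45)/110) = 0.0657.
  - Without continuity correction: Φ((0.200 − 1.96 × 0.0671)/0.0657) = 85.1%.
  - With correction: Φ((0.200 − 1/110 − 1.96 × 0.0671)/0.0657) = 81.7%. Fisher's exact test gives 81.6%. Stated: 82%.

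Both figures stand.

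**Step 2: baseline adjustment for PC-QOL at 110 per arm.** Unadjusted SE = 1.05 × √(2/110) = 0.142. Adjusted SE = 0.142 × √(1 − r²), ignoring the few degrees of freedom spent.

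| r (assumed) | Variance saved | SE | 95% half-width | Equivalent N = 220/(1 − r²) |
|---|---|---|---|---|
| 0 | 0% | 0.142 | 0.278 | 220 |
| 0.3 | 9% | 0.135 | 0.265 | 242 |
| 0.5 | 25% | 0.123 | 0.240 | 293 |
| 0.6 | 36% | 0.113 | 0.222 | 344 |

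The half-width shrinks by about 5% (0.265/0.278) to 20% (0.222/0.278). Power for a difference of 1 already exceeds 99.9% without adjustment.

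**Step 3: strata and the cough-free outcome.** Two ages by five sites give 10 cells. Splitting Darwin by Aboriginality adds 2, making 12, or about 220/12 ≈ 18 children per cell on average. Simulations used 12 strata, blocks of 4 or 6 and n = 220, with assumed stratum effects on the log-odds scale.

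- Type I error of the unstratified chi-squared test: about 4.5% at SD 0.4, falling to about 3.0% at SD 1.0. A stratified test stays near 5%.
- Power with marginal rates held at the planned 35% and 55%, from one such run with unequal stratum sizes:

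| Log-odds SD (assumed) | Unstratified | Stratified | Loss (points) |
|---|---|---|---|
| 0.4 | 85.6% | 86.2% | 0.6 |
| 0.7 | 86.7% | 88.0% | 1.3 |
| 1.0 | 86.1% | 89.4% | 3.3 |

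Allowing for simulation and set-up differences, the loss is about 1 to 4 points. SD 1.0 is a strong assumption: strata one SD either side of the mean then differ e² ≈ 7.4-fold in odds.

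**Step 4: strata and the t test.** By simulation, type I error is about 5.2%, 4.3%, 3.7% and 3.4% when strata explain 0, 5, 10 and 20% of the variance. This is again conservative.

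**Step 5: the switch.** The sizing quantity is a difference in means. A rank test has no parameter equal to that difference unless further assumptions are made. At about 110 per arm, a comparison of means with robust standard errors does not need normal data, so the switch buys little.

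**The case against.** The best defence is that nothing here is invalid. Unadjusted tests after stratified randomisation are unbiased, with type I error at or below nominal. PC-QOL needs only 50 children for its stated power and will have about 220, so a narrower interval is unlikely to alter the conclusion at the planned effect. All the gains rest on assumed inputs. The article is also condensed, and covariate adjustment is often settled in a SAP.

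Most of this stands and sets the size of the point. The last argument does not remove it: the article names its tests, so a SAP that follows the text would inherit them.

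Four stronger readings are tempting but unsupported:

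- *The tests are biased or the sample size is wrong.* Neither holds; type I error is not inflated and both stated powers reproduce.
- *Ignoring strata drags cough-free power down to about 72%.* That figure appears when the conditional odds ratio is held fixed while stratum spread grows, which shrinks the marginal difference (to 16.7 points at SD 1.0). At the planned 35% v 55%, unstratified power stays near 86–87%.
- *Neither primary estimate is fixed.* The cough-free difference in proportions is untouched by the switch. For PC-QOL the article still promises a difference with a 95% interval; the switch replaces the test. What remains is a possible mismatch between test and estimate.
- *Week-6 PC-QOL will be skewed.* A pile-up near the maximum of 7 is plausible, but no distribution is shown, and resolution includes improvement of at least 75%, so resolved children need not score at the ceiling.

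**Conclusion.** The point holds as one of efficiency and consistency, not validity. The protocol forgoes precision that data already being collected would provide.

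- **PC-QOL:** SE 0.142 could be 0.135–0.113, given r = 0.3–0.6. The benefit is a tighter interval around the estimate, useful when judging it against the 1-point threshold.
- **Cough free:** mild conservatism and about 1 to 4 power points lost, given a stratum log-odds SD of 0.4–1.0 and the planned rates. If the strata are not prognostic, nothing is lost.
- **Normality switch:** if triggered, the PC-QOL test would no longer address the mean difference used for sizing. Whether it would be triggered cannot be told from the document.

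The direction of the first two is sure if baseline and strata are prognostic; their size depends on the assumed ranges.

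**What to change.** Specify one primary model per outcome before unblinding.

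- **PC-QOL at week 6:** linear regression on arm, baseline PC-QOL, age stratum, site and Darwin Aboriginality, with robust standard errors. Report the adjusted mean difference and 95% CI whatever the distribution, and drop the switch from the primary analysis.
- **Cough free at week 6:** Mantel-Haenszel stratified test and risk difference with 95% CI over the randomisation strata. With about 18 children per cell on average, write a pooling rule for sparse strata and fix it before unblinding.
- **Sensitivity analyses:** keep the unadjusted t, rank and chi-squared tests.

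The cost is analysis-plan wording and minor programming. No new data are needed, and the sample size does not change.
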